## Abstract

**Background:**

An increase in sexually transmitted infections (STIs) as well as an increase in the use of new information and communication technologies among young people in Catalonia is the inspiration behind the idea of designing a smartphone app to promote partner notification of STIs.

**Objective:**

The main objective of this study is to design a Web-based tool adapted to smartphones for partner notification of STIs among youth who are 16 to 24 years old. Additionally, the objective is to evaluate the Web-based tool’s role in increasing the *patient referral* partner notification.

**Methods:**

This is a multicenter randomized controlled trial with a proportional stratification of the sample by center and random allocation of participants to the 3 arms of the study (simple Web-based intervention, game Web-based intervention, and control). This study is being conducted by midwives, gynecologists, and physicians in the sexual and reproductive areas of the primary health care centers.

**Results:**

The primary outcome measure is the number and proportion of partner notifications. Additional outcome measures are the yield of early diagnosis and treatment of those exposed and infected, acceptability, barriers, and preferences for partner notification.

Expected results include an increase in the yield of partner notification, early diagnosis and treatment among youth using Web-based interventions compared with those receiving the traditional advice to notify, and a description of sexual networks among those participating in the study.

**Conclusions:**

The *Notijoves* is expected to have a sustainable positive impact in the partner notification practice among youth and contribute to increasing the awareness of STI prevention.

**International Registered Report Identifier (IRRID):**

DERR1-10.2196/12896

## Introduction

### Background and Study Rationale

Prevalence of sexually transmitted infections (STIs) among young people has increased over the years. In Catalonia, prevalence of *Chlamydia trachomatis* among those below 25 years increased from 5.8% in 2008 to 8.5% in 2013 [1]. The most affected age group is the 16 to 18 years old.

The main rule to control communicable diseases is guaranteeing an early detection of the infected to treat them and alert the exposed [2]. Therefore, sexual partner notification is crucial to reach awareness of the exposed and facilitate testing for potential diagnosis. Scientific evidence highlights the need to improve partner notification and early testing [3-5], and in the case of *Chlamydia trachomatis,* partner notification is proved to be more cost effective than systematic screening [6,7]. Partner notification is recognized to be crucial for reducing transmission and preventing reinfection at an individual level [3].

In our country, as well as in most of the other European countries, the most frequently used models of partner notification are the ones done by the patient itself *(patient referral)*, and the one done by the health professional after obtaining the patient’s approval *(provider referral)* [8].

An internet-based system of partner notification allows the anonymous practice through a Web-based notification, an email, or short messaging system. This tool may help in getting in touch with previous sexual partners with whom there is no interest to revisit in person.

In addition, the introduction of a gamified approach of partner notification among youngsters is an innovative way to involve those who otherwise would not be interested in notifying. By discovering through gamification the main aspects of the STI that the youngsters were diagnosed with and the importance of notifying partners for the prevention of further transmission, the youngsters are more likely to notify their partners about a potential infection, and they are more likely to advise them to get tested for the potential infection.

Provided that youngsters are prone to using new technologies and video games and that previous studies prove the utility of gamification as an important tool to promote behavior changes [9-12], we propose to include this gamification as a third arm of the trial.

This study also includes the social network analysis that allows for a deep study of the relationships among young people. It is based on the evidence that transmission of sexual infections in a social group is determined by the existence of central members within the social structure [13]. Therefore, we aim to conduct a randomized controlled trial to assess the effectiveness of partner notification through the use of new information and communication technologies (ICTs). Our hypothesis is that the percentage of partners informed by their index cases will be higher when the index cases can use new technologies (personally or anonymously) compared with the use of paper notification card to do a *face-to-face* partner notification, without any specific guidance.

### Development of an App to Promote Patient Referral Partner Notification

According to the Report of the Spanish Digital Society, 2017, 86% of the youngsters aged 15 to 24 years own a smartphone, and this has become their main means of communication. It is expected that in 2018, 50% of these youngsters will exclusively use smartphones to be on the Web [14]. In addition, these youngsters are heavy users of smartphone apps. Making available a responsive smartphone app that helps to do partner notification, either personally or anonymously, may increase partner notification practice. New and innovative ways of addressing partner notification in a sustainable way that can benefit youngsters and reduce transmission are a high priority. That is why we proposed the development of a smartphone app in Spanish and in Catalan (see Figure 1 for app icon in Spanish). Experts in gamification and Web app contributed to its development, drawing on the gamification-information- motivation-behavioral skills approach to behavioral change [15].

A total of 3 workshops with youngsters of different social levels were conducted by a psychologist, anthropologists, and nurses to identify the best way to design the game.

The app contains different story games that are sensitive to sexual orientation of youngsters, adapted information to the STI that was diagnosed to the patient, and choice of different methods to do partner notification (short message service, email, WhatsApp, or face to face), either anonymously or by identifying himself or herself. At the end of the game, the youngsters will have learned preventive features of the infection, and they should be motivated to inform all sexual partners exposed to the STI; in addition, they will choose a method to send them the message or inform them personally.

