#### Game Intervention Group

Those advised to enter the *Notijoves* Web app with a code and follow the steps of the game to finally choose among different ways to notify their partners.

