### Web App Game Intervention Group

Individuals assigned to this group receive an Information sheet explaining the objectives and procedures of the study. After providing a signature of their informed consent, they receive a paper copy of this informed consent that has a specific code through which they enter the game by connecting to the *Notijoves* Web address. A paper card with the “Notijoves” Web address is given to the patients. Once they enter the Web app, they are asked to feed the given code into the field of Young PANDORA screen.

By entering the code, they start playing the game, and they are directed through different screens and situations. A Web-based questionnaire is inserted in the game. At the end of the game, they are also asked to respond to a satisfaction questionnaire.

The game is expected to motivate the youngster to notify partners of their exposure to an STI. While playing the game, the youngsters are asked to answer questions related to the clinical symptoms, prevention, and control of their recently diagnosed STI. Like this, they *learn by playing.* Another feature of the Web app is the link to advisory videos on how to approach the *face-to-face* notification of exposure to an STI. Finally, the game ends with a screen, where the youngsters can choose from among the different electronic tools to notify (short message service, email, or WhatsApp) either anonymously or by identifying themselves.

The electronic partner notification card has the following: (1) a code automatically assigned by the electronic system that is concordant with the arm where the index case patient entered the study, (2) the informative message advising the partner to visit a health center for diagnosis and potential treatment, and (3) a link to a list of health centers of the study and the Web app address, where the partner could go and where the informed partner could enter and participate in the study by introducing the code. Along with the notification card, the partner receives an electronic letter to be given to the health professional for him to be aware of the STI diagnosed to the sender of this notification and the advised treatment.

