### Web App Direct Notification Intervention Group

Individuals assigned to this group receive an Information sheet explaining the objectives and procedures of the study. After providing a signature of their informed consent, they receive a paper copy of this informed consent that has a specific code through which they enter the *Notijoves* Web address. A paper card with the *Notijoves* Web address is given to the patients. Once they enter the Web app, they are asked to feed the given code into the field of Young PANDORA screen (see Figure 3). By entering the code, they are directed to a Web-based questionnaire and are offered an option to choose from among the different electronic tools (short message service, email, or WhatsApp) to notify either anonymously or by identifying themselves. Finally, they are also asked to respond to a satisfaction questionnaire.

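### Face-to-face notification is an app option in one section but missing from the arm descriptions, and app-arm partners told in person have no described way to carry a study code

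*Protocol article*

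**What the plan says.** The protocol article describes the app's notification options in three places.

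- **Development of an App to Promote Patient Referral Partner Notification:** the app offers a "choice of different methods to do partner notification (short message service, email, WhatsApp, or face to face". At the end of the game, users are told that "they will choose a method to send them the message or inform them personally".
- **Groups of the Study:** the wording is open. Game-arm users "follow the steps of the game to finally choose among different ways to notify their partners", and the direct arm is worded in much the same way.
- **Web App Game Intervention Group** and **Web App Direct Notification Intervention Group:** the choice is electronic. Game-arm users "choose from among the different electronic tools to notify (short message service, email, or WhatsApp) either anonymously or by identifying themselves". Direct-arm users "choose from among the different electronic tools (short message service, email, or WhatsApp) to notify". The game section also mentions "advisory videos on how to approach the *face-to-face* notification of exposure to an STI".

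On codes, the electronic card in the app arms carries "a code automatically assigned by the electronic system that is concordant with the arm" of the index case. The control-arm procedure (the Control Group section after Participation Procedure) gives each paper card a code matching the index case's arm.

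The section on what happens to partners says that those who attend without the letter and code cannot be linked and are lost to follow-up. If they prove infected, they enter as new index cases with a new random code. The main outcome is the percentage of partners informed by their index cases, by study group.

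**The concern.** There are two linked problems. First, the article does not settle whether in-person notification is part of the app intervention. Second, if it is, or if app users do it anyway after watching the face-to-face videos, the plan describes no means of tracing it in the app arms. In-person notification with a coded paper card is the ordinary control route.

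The primary comparison is between arms in the proportion of partners informed. If one type of notification can be traced in control but not in the app arms, part of any observed difference reflects how notifications were captured rather than how many occurred. The new-index-case rule adds to this: an infected partner of an app-arm index case, told in person and attending without a code, may be allocated to a different arm and counted there as an unrelated participant.

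**Working it through.** The plan gives no figure on this point to reproduce, so the check is mainly a comparison of sections.

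**Step 1. Is face to face an app option?**

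| Section | Options described |
|---|---|
| Development of an App | SMS, email, WhatsApp, face to face |
| Groups of the Study (both app arms) | Various ways, not specified |
| Web App Game Intervention Group | Choice screen: SMS, email, WhatsApp; videos on telling a partner in person |
| Web App Direct Notification Intervention Group | Choice screen: SMS, email, WhatsApp |

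The first row conflicts with the last two on what is offered at the point of choice. The second row does not resolve it.

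**Step 2. What does a partner told in person hold?**

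| Arm | Coded item described for a partner told in person |
|---|---|
| Control | Paper card with arm-matched code |
| Game app | None; the code is on the electronic card |
| Direct app | None; no other coded item is described |

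**Step 3. What happens without a code?** The partner cannot be linked to an index case and is lost to follow-up. If infected, the partner is randomised as a new index case.

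**Step 4. Does another instrument capture it?** Under Data Collection:
- The index-case questionnaire asks about intention to inform (all, some, none, do not know), not about notifications made.
- The satisfaction questionnaire asks whether the anonymous option was used, not which partners were told in person.
- The recipients' questionnaire has a face-to-face answer, but without a code that answer cannot be tied to an index case or an arm.

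**Step 5. What follows for the primary percentage?** Suppose only app-sent or coded notifications count. This is an assumption, because the article does not state the counting source. Let p_A and p_C be the true proportions informed in an app arm and in control, and f the share of informed app-arm partners told in person without a code. Then:

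- counted app proportion = p_A × (1 − f)
- loss from this mechanism alone = p_A × f

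Neither p_A nor f is in the document. For an assumed p_A of 60%:

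| f (assumed) | Counted | Loss |
|---|---|---|
| 0% | 60% | 0 points |
| 10% | 0.60 × 0.90 = 54% | 6 points |
| 20% | 0.60 × 0.80 = 48% | 12 points |
| 30% | 0.60 × 0.70 = 42% | 18 points |

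This is a gross loss in one arm, not the net bias. Limitations describes control partners lost because they attend outside the study area (share g, say) and false anonymous notifications that inflate yield (h points in an app arm, say). With these included:

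- net bias in (app − control) = −p_A × f + h + p_C × g

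The first term is negative and the other two are positive. The document gives no value for f, g or h, so the sign of the sum is not determined.

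**The case against.** The case on the other side is substantial.

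- **The contradiction is softer than it looks.** The lists in the two arm sections expand the term electronic tools, which could not include face to face. Neither section says that in-person notification is unavailable, and Groups of the Study leaves the options open. This stands in part. The development section nevertheless presents face to face as a method the app offers, and neither description of the choice screen shows it.
- **The missing code is inferred from silence.** This is a condensed article and its participation algorithm figure is not shown. That is fair, and it is why the point is that no route is described, not that none exists. Control paper cards are coded, so it would also be wrong to say that codes exist only on the electronic card in the trial as a whole.
- **The outcome is partners informed, not coded attendance.** Its source could be app records, index-case report or attendance. This stands: one cannot say that app-arm partners told in person cannot be counted. If the app logged a face-to-face choice, however, that would record a plan to notify and would not be comparable with a card presented by a partner.
- **Control loses partners too.** A control partner told verbally, or attending without the card, is equally unlinkable, and Limitations describes biases that favour the app. This stands and removes any claim about net direction. The difference that remains is that a control partner told in person can hold a code, whereas no means is described for an app-arm partner to do so.

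A reader might also infer a bias of game against direct, because the face-to-face videos appear only in the game section. The documents do not support that. The text introduces them with "Another feature of the Web app is the link to advisory videos on how to approach the", which attributes them to the app rather than to the game, and the direct-arm section is merely silent.

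**Conclusion.** The point holds as an unreconciled description of the intervention combined with arm-dependent traceability of in-person notification. Taken alone, the mechanism under-counts the app arms by p_A × f under a rule that counts only app-sent or coded notifications. Both quantities are unknown, and the 6 to 18 points shown above rest entirely on assumed inputs.

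A reader might go further and infer that a true benefit of the app would be recorded as harm. For example, an assumed 50% against 40% becomes 0.50 × 0.70 = 35% against 40% if 30% of informed app-arm partners are told in person without a code. That reversal depends on the chosen rates and on complete capture in control, which the loss rule for partners without codes and the Limitations section both contradict. Net sign and size cannot be derived from the document.

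The matter still deserves a change rather than a note. It touches the primary outcome, Limitations does not mention it, and none of the questionnaires described repairs it.

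**What to change.** Reconcile the development section with the two sections that describe the app arms in operation.

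- **If face to face is an app option:** add it to both arm descriptions. When a user chooses it, have the app issue one coded card per partner, on screen or as a printout, in both app arms. Count these cards by the same rule as the control paper card.
- **If it is not an option:** remove it from the development section.

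The cost is a wording correction and, in the first case, a small app change, since the system already assigns codes to electronic cards. The drawback is that index cases enrolled before the change will not have the card. Results reports 32 participants by early June 2018 and about 6 recruitments per month after that, so the date of the change should be recorded to identify them. A sensitivity analysis using the face-to-face answer in the recipients' questionnaire would not make good the gap, because partners without a code cannot be assigned to an index case or an arm.

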**Figure 1 figure1:**
[figure not shown]
App icon “in Spanish”.

### Aims and Objectives

The aim of this study is to describe the protocol for the randomized controlled trial of the *Notijoves* Web-based tool, adapted to smartphones for partner notification of STIs among youngsters aged 16 to 24 years.

The first objective of the study is to design the tool and evaluate its role in increasing partner notification done by the patient (patient referral partner notification) for all eligible sexual partners.

The specific objectives are the following:

Describe sociodemographic characteristics of index cases and consecutive sexual partnersDescribe coinfections within the groupDescribe acceptability, barriers, and preferences for executing partner notification using ICTsEvaluate the utility to apply the game theory (gamification to promote behavior change) in the design of a Web app for partner notification of STIsEvaluate the yield of ICTs for partner notification of STIs among sexual partnersAssess the impact of ICTs in primary transmission of STIsDescribe the characteristics of the social and sexual network among youngsters

## Methods

### Design

This is an unblinded 3-armed randomized controlled trial, assigning patients to each arm of the study through the proportionally stratified sample of patients by health center, which will test the primary hypothesis that a greater proportion of partners will be informed about their exposure to STIs (syphilis, chlamydia, or gonococcus) in the intervention groups compared with the control group. We will randomize 416 young and recently diagnosed index cases in 1 of the 7 centers of the study. The researcher responsible for analyzing the data will be blind to group allocation.

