### Sample Size

Young population accessing all centers of study within a year is around 400. They have been randomly distributed in 3 arms, according to the Bonferroni correction, to allow multiple comparisons of outcomes with a significance level of *P*=.016. The trial is expected to have 10% of withdrawals after recruitment within the intervention groups and 20% of withdrawals after recruitment within the control group. Therefore, to have at least 120 participants in each 1 of the groups, 133 are recruited in each 1 of the intervention groups and 150 are recruited in the control group. The random list ratio is 1:1:1.28. To achieve this sample, participant recruitment is allowed for a period ranging from 13 to 18 months.

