### Data Analysis

Descriptive analysis of index cases visiting health centers will be baselined to further assess differences in yield by groups. Chi-square test and Student *t* test for categorical and continuous variables will be used to assess differences in baseline characteristics among groups. Regression analysis and adjusting for confounding variables will be used to evaluate the primary outcome and relative risk, and its 95% CIs will be calculated. Significance will be set at .05. The multiple imputation method will be used to generate possible values for missing values. This is considered the gold standard for dealing with missing values. Data will be analyzed in Stata v12 (StataCorp LLC).

The methodology of analysis of the social and sexual networks will be used from an egocentric perspective. Structural measures of the network will be calculated, such as the size of the network, number of direct links, density, the geodesic average distance, diameter of ego’s network, and measures of centrality, such as the degree of intermediation of a contact or index case. Furthermore, we will compare social network, density, and structure. Network measurements will be done using the R statistical package.

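### The primary hypothesis does not say how the two web arms are set against control, and the plain Bonferroni rule at .016 costs power that a step-down test at the same 5% family-wise error would keep

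*Protocol article*

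**What the plan says.** The Design section describes the study: "This is an unblinded 3-armed randomized controlled trial". Its primary hypothesis reads: "a greater proportion of partners will be informed about their exposure to STIs (syphilis, chlamydia, or gonococcus) in the intervention groups compared with the control". The Background and Study Rationale section words the hypothesis as a notification percentage that "will be higher when the index cases can use new technologies (personally or anonymously) compared with the use of paper notification card". The abstract expects a higher yield "among youth using Web-based interventions compared with those receiving the traditional advice to notify". None of these says how the two web arms enter the test.

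The Main Outcome Variable section defines the outcome by assigned study group. The Sample Size section sets a multiplicity rule: participants were distributed over three arms by Bonferroni "to allow multiple comparisons of outcomes with a significance level of *P*=.016". The comparisons are not listed. The value of gamification appears under Aims and Objectives as a specific objective, not as part of the primary hypothesis. The Data Analysis section says "Significance will be set at .05" and does not mention Bonferroni.

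**The concern.** Two things need attention.

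- **The rule for success is open.** The phrase "in the intervention groups compared with the control group" can mean each arm judged on its own, the two arms pooled, or both arms required to win. The same data can pass under one reading and fail under another.
- **The multiplicity rule is stricter than it needs to be.** A level of .016 implies three comparisons, while the primary hypothesis holds at most two contrasts with control. Whichever family is intended, plain Bonferroni ignores that once one comparison is rejected, fewer null hypotheses can still be true. A step-down test uses this and keeps the same error control.

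Power matters here. The Results section reports about 6 recruitments per month, slower than expected, so lost power cannot easily be made up with more patients.

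**Working it through.** **1. Reproducing the stated level.** Bonferroni is .05/k: k = 2 gives .025, k = 3 gives .0167, k = 4 gives .0125. Only k = 3 fits the stated .016, and then by truncation. Three arms form three pairs: game–control, direct–control, game–direct.

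**2. Can the open success rule change the verdict?** Illustrative counts, 120 per arm (Sample Size section), two-sided pooled-variance z test, all judged at .016:

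- Control 48, game 68, direct 54. Game vs control: .5667 − .4000 = .1667; SE = √(.4833 × .5167 × 2/120) = .0645; z = 2.58, p = .0098, rejected. Pooled web vs control: .5083 − .4000 = .1083; SE = √(.4722 × .5278 × (1/240 + 1/120)) = .0558; z = 1.94, p = .052, not rejected.
- Control 60, game 76, direct 76. Pooled: .6333 − .5000 = .1333; SE = √(.5889 × .4111 × (1/240 + 1/120)) = .0550; z = 2.42, p = .015, rejected. Each arm alone: SE = √(.5667 × .4333 × 2/120) = .0640; z = 2.08, p = .037, not rejected.

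The verdict can turn either way at one common level. With true rates 40/55/55%, pooled and either-arm readings, both at .016, disagree in about 10% of simulated trials; either-arm and both-arm readings disagree in about 34%.

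**3. Power of one web arm vs control at a fixed level.** Assumed rates 40% and 55%, 120 per arm, one binary result per index case.

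- SE under the null: √(2 × .475 × .525/120) = .0645. SE under the alternative: √((.40 × .60 + .55 × .45)/120) = .0637.
- Power = Φ((.15 − z × .0645)/.0637).
- At .016, z = 2.409: Φ(−.083) = 47%.
- At .025, z = 2.241: Φ(.086) = 53%.
- At .05, z = 1.960: Φ(.371) = 64%.

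Holm over two contrasts tests at .025 or .05, so its power must lie between 53% and 64%. Shaffer over three pairs tests at .0167 or .05, so its power must lie between 47% and 64%.

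**4. Why the second step may use .05.** Holm with two hypotheses tests the smaller p at .025 and, if that is rejected, the other at .05. Among three pairwise equalities, if one is false at most one of the other two can be true, because two true equalities would force the third. Shaffer therefore tests the smallest p at .0167 and, if that is rejected, the other two at .05 each.

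**5. Simulated power** (120 per arm, same z test):

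| True rates control/game/direct | Target | Bonferroni .016 | Shaffer, three pairs | Holm, two contrasts |
|---|---|---|---|---|
| 40/55/55% | one arm vs control | 47% | 55% | 58% |
| 40/55/55% | both arms vs control | 31% | 45% | 46% |
| 30/45/45% | one arm vs control | 50% | 58% | 62% |
| 50/65/65% | one arm vs control | 48% | 55% | 59% |
| 40/60/40% | game vs control | 77% | 83% | 81% |

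With all rates at 40%, the simulated family-wise error is about .04 for Bonferroni, .04 for Shaffer and just under .05 for Holm. All stay below 5%.

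Shaffer's first step (.0167) is practically the Bonferroni level, so a first rejection is no easier. Its gain comes from the second step. Holm also eases the first step, to .025.

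**The case against.** The case for the plan is substantial, and much of it stands.

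- **Bonferroni over three pairs is valid.** It controls the error rate and gives simple simultaneous intervals. This stands: the point is an efficiency gain, not an error. The Data Analysis section, however, announces 95% intervals, so the article does not appear to use that advantage.
- **The documents lean towards arm-by-arm tests.** The outcome is defined by assigned group, the hypothesis uses the plural, and a single pooled contrast would need no Bonferroni correction. This stands, and it is why the fix proposes separate contrasts. A reader might infer that the article describes three different deciding contrasts. It does not: the wordings in the Background and Design sections are compatible, and no section states a pooled test.
- **The alpha share is inferred.** A reader might conclude that a third of the alpha is certainly spent on game against direct, outside the hypothesis. All three pairs is the natural reading of .05/3 with three arms, but another set of three would give the same figure. Even if that pair is included, gamification is a stated objective, and testing it is a legitimate choice.
- **Success rules are often left to an analysis plan.** One may exist and settle the question. But the article itself fixes both the hypothesis and the Bonferroni rule, and the power cost follows from that rule.
- **Pooled power at .05 (about 77%) against one-arm power at .016 (47%) is not a fair comparison.** It mixes two levels, and a trial-level rule with a single-arm one. At a common .016, pooled and either-arm power are close, about 61% and 64%. That contrast is not used here.

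**Conclusion.** The point holds in a limited form. The primary hypothesis leaves the role of the two web arms open, and the stated plain Bonferroni rule is valid but less powerful than a step-down with the same 5% family-wise control. With 40/55/55%, the gain for one web arm against control is about 8 points with Shaffer (47% to 55%) and 11 with Holm (47% to 58%). For both arms together it is about 14 to 15 points (31% to 45–46%).

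The sizes rest on assumed rates, 120 analysed per arm, and one independent binary result per index case. The actual outcome is a percentage of partners, and clustering of partners within index cases is ignored, so the absolute powers are illustrative. The ordering against Bonferroni does not depend on the rates, because Shaffer over the three pairs and Holm over the two control contrasts each reject everything that Bonferroni at .016 rejects within their family. The difference between .016 in the Sample Size section and .05 in the Data Analysis section is a separate mismatch. This point would remain if one level were agreed.

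**What to change.** - **Sample Size:** list the comparisons behind .016. This comes first, because Shaffer's second step relies on the three comparisons being the three pairs.
- **Design:** state that each web arm is compared with control, and that the hypothesis is met for each arm whose contrast is rejected in favour of that arm. Align the Background wording with this.
- **Sample Size and Data Analysis:** replace plain Bonferroni with a step-down at family-wise two-sided 5%, stated the same way in both sections.
  - If all three pairs stay confirmatory, use Shaffer: smallest p at .0167 and, if rejected, the other two at .05 each.
  - If the family is limited to the two control contrasts, use Holm: smaller p at .025 and, if rejected, the other at .05. Game against direct becomes a secondary test of the gamification objective.

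The choice of family is the sponsor's. The change is wording, made before the data are analysed, with no extra patients or data. The cost is that simultaneous confidence intervals matching a step-down are less simple than Bonferroni intervals; under the Holm option, game against direct also loses its confirmatory place.
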